
### Statistical analysis

The effect of the intervention on all participants will be assessed based on intention-to-treat and per-protocol analyses. The data will be checked for plausibility by randomly checking the accuracy and completeness and source data verification. The normality of continuous variables will be determined using a Kolmogorov–Smirnov test. Appropriate statistical transformation (logarithmic transformation, square root transformation, cube root transformation, or reciprocal transformation) will be used for continuous variables with not normal distribution.

Hence, statistical analysis for continuous variables with normal distribution (parametric tests) will be used in this study.

Continuous variables with normal distribution and transformed variables will be expressed as mean ± SD. Categorical data will be presented as frequency (percentage).

To compare the mean differences within each group, before and after intervention, the paired t-test will be used for continuous variables.

For continuous variables, one-way analysis of variance (ANOVA) will be used to detect differences in sociodemographic characteristics, metabolic profiles, physical activity levels, and dietary intakes at the study baseline between the four groups.

Categorical data at the study baseline will be analyzed using the Chi-squared test between the intervention groups.

Repeated measures analysis of variance (RM ANOVA) with Bonferroni procedure to adjust for the five comparisons will be used to assess time effects and time-by-treatment (vitamin D and/or omega-3) interaction effects on all outcome variables between groups.

Since we have multiple endpoints and we will compare five pairwise comparison, all *p* values will be corrected using the Bonferroni adjustment method.

Two-way RM ANOVA with Bonferroni adjustment for comparisons will be used to assess the relationship between changes in mean serum vitamin D level and each of fasting blood sugar and other outcome variables between groups.

Levenes test for independent data in one-way ANOVA and Mauchly’s test in RM ANOVA will be used to test homoscedasticity.

All statistical measurements will be reported with 95% confidence intervals (CI). A *p* value < 0.05 will be considered statistically significant. All statistical analyses will be performed using SPSS version 24.

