### Inclusion criteria

Women of reproductive age (aged 15–50 years);FBS 100–125 mg/mL [1, 2, 25];Vitamin D < 32 ng/mL [26];BMI < 30 kg/m^2^.

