### Study participants

Women of reproductive age with prediabetes from Karaj health centers diagnosed with FBS test (fasting glucose 100–125 mg/mL) [1, 25] will be invited to this study.

The study investigator will call participants by phone and will screen them according to the inclusion and exclusion criteria.

Eligible participants will be referred to the Shahid Rastravesh Health Center. First, the goals, methods, and benefits of the intervention will be explained by the investigator and the informed consent form will be signed by participants. At the beginning, 10 mL of blood will be taken from a peripheral vein after a 12-h overnight fast to assess plasma glucose levels, insulin, TG, HDL-C, TC, and vitamin D. After centrifuging for 10 min (3000 rpm), the serum samples will be frozen simultaneously and stored at − 80 °C until analyzed [12]. LDL-C will be estimated based on the Friedewald equation [27]. Participants will receive a three-day food record. The investigator will explain how to complete the form to each participant.

After three days, women who have been confirmed as having prediabetes (fasting glucose 100–125 mg/mL) and hypovitaminosis D (vitamin D < 32 ng/mL) [26] will be invited to the Shahid Rastravesh Health Center.

The sociodemographic characteristics questionnaire, short-form International Physical Activity Questionnaire (IPAQ), DASS-21, and PSQI will be completed with interviews. The investigator will review completed three-day food record in presence of each participant.

Anthropometry including weight, height, and waist circumference will be measured using a digital scale, stadiometer, and non-elastic tape, respectively.

Blood pressure (systolic and diastolic) will also be measured with a digital manometer.

All the above-mentioned stages, including blood sampling, completing four questionnaires (three-day food record, IPAQ, DASS-21, and PSQI), anthropometric measurements and measuring blood pressure, will be repeated after eight weeks.

At the end, the evaluated outcomes will be presented to participants privately. A Data Monitoring Committee (DMC) will also monitor during and at the end of this study (Fig. 2).

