Weight, height, and waist circumference will be determined using a digital scale, stadiometer, and non-elastic tape, respectively. They are measured thus: weight without shoes, with minimal clothing, and with a 100-g accuracy (Beurer, BF220, Germany); height without shoes, standing, heels against the wall, flat and forward head, and with 0.5-cm accuracy (Seca, Hamburg, Germany); and waist circumference with minimal clothing, midway between the last rib and the iliac crest. BMI will be calculated using the height and weight measurements kg/m^2^ [12].Systolic and diastolic blood pressure values will be measured with a digital manometer (Beurer, Germany). Values will be recorded in mmHg [30] .Physical activity will be investigated the short form of IPAQ [31]. The IPAQ form comprises walking, moderate intensity, and vigorous intensity activity and will be expressed as metabolic equivalents per minute (MET min) per week. The levels of physical activity will be categorized into low, moderate, and high based on the IPAQ criteria. This questionnaire has been validated in previous studies [32] including in Iran [33].Food intake status will be assessed using the three-day food records (comprising two working days and one weekend). Modified Nutritionist-4 software program (First Databank, San Bruno, CA, USA) will be used to estimate the energy and nutrient intakes.DASS-21 and PSQI will be applied to assess psychological distress [34, 35].DASS was designed to measure emotional distress in three subcategories [34] of depression (e.g. loss of self-esteem/incentives and depressed mood), anxiety (e.g. fear and anticipation of negative events), and stress (e.g. persistent state of over arousal and low frustration tolerance).DASS is a self-report scale with 21 items (seven items for each category) based on a 4-point rating scale. To calculate comparable scores with full DASS, each seven-item scale will be multiplied by two. Participants will be asked to explain times of occurrence of each item (in the form of statements) over the past week, with “0 = did not apply to me at all” to “3 = applied to me very much, or most of the time.” The higher score shows more severe emotional distress. Validity and reliability of the DASS-42 were examined in several studies and in Iranian samples [36–38].The PSQI is a self-report questionnaire that assesses sleep quality and quantity [35]. The19-item self-report questionnaire yields seven component scores: subjective sleep quality; sleep latency; sleep duration; habitual sleep efficiency; sleep disturbances; use of sleeping medication; and daytime disfunction.There are five additional questions. These are not used in the scoring. A Global Sleep Quality score > 5 indicates poor sleep quality. There is evidence of the reliability and validity of the PSQI in several subjects [39–42] and also in Iran [43, 44].

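### A Kolmogorov–Smirnov test on the variables, not on residuals or paired differences, decides the analysis scale; it can react to the FBS entry window, and two listed transformations are undefined at zero DASS-21 scores

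*Protocol article*

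**What the plan says.** The protocol article, Statistical analysis, sets out a chain of three steps.

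- The trigger: "The normality of continuous variables will be determined using a Kolmogorov–Smirnov test".
- The action for variables that fail: "Appropriate statistical transformation (logarithmic transformation, square root transformation, cube root transformation, or reciprocal transformation) will be used". No criterion is given for choosing among the four functions, and nothing is said about zeros.
- The consequence: "Hence, statistical analysis for continuous variables with normal distribution (parametric tests) will be used in this study". Results are then summarised as follows: "Continuous variables with normal distribution and transformed variables will be expressed as mean ± SD".

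The analyses that follow are a paired t-test within each group and a repeated measures ANOVA for time and time-by-treatment "interaction effects on all outcome variables between groups". Both need the baseline and week-8 values of an outcome on one scale.

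Two other parts of the article bear on this. Inclusion criteria require "FBS 100–125 mg/mL", and Study participants applies the same window to the baseline blood sample, admitting only "women who have been confirmed as having prediabetes (fasting glucose 100–125 mg/mL"). Nothing restricts FBS at week 8. Assessments and measurements scores DASS-21 items from 0, labelled "did not apply to me at all".

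**The concern.** The models named in the plan assume roughly normal residuals or paired differences. They do not assume that the raw values of each variable are normal. A trigger based on the variables can therefore fire when the model is sound, or stay silent when it is not.

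FBS is the primary outcome, and its baseline distribution is cut at both ends by design. A normality test may register that cut, which is an eligibility rule and says nothing about the model. If the test is run visit by visit, baseline can fail while week 8 passes, and the rule then does not say on which scale the pair is to be analysed. If a transformation is adopted, the primary effect may be summarised in units that no clinician uses.

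For DASS-21 the risk is selective loss. Two of the four listed functions have no value at zero, so the women with the lowest distress could drop out of an analysis described as intention-to-treat.

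**Working it through.** **Inputs from the article.** Entry window 100–125; 168 women in four equal groups, so 168 / 4 = 42 per group; the four listed transformations; DASS-21 items scored from 0, with each seven-item sum doubled. The plan states no figure on this point, so there is none to reproduce.

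**Inputs assumed.** The article does not give the FBS distribution in this population. Baseline FBS was taken as a normal variable with the parent mean and SD shown below, cut to 100–125 and not rounded. Week-8 FBS was baseline plus a normal change with mean −3 and SD 3 to 10.

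**Test.** Kolmogorov–Smirnov statistic with mean and SD estimated from the sample, at 5%. It was run with the Lilliefors correction (critical value 0.0690 at n = 168 and 0.1354 at n = 42) and with the ordinary uncorrected critical value. The article does not say which version applies, or whether the test is pooled or per group.

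**Step 1. Share of simulated trials in which raw baseline FBS is flagged.**

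| Parent mean (SD) | Pooled, corrected | Pooled, uncorrected | Per group, corrected | Per group, uncorrected |
|---|---|---|---|---|
| 90 (10) | 1.00 | 0.94 | 0.70 | 0.05 |
| 95 (10) | 1.00 | 0.76 | 0.59 | 0.03 |
| 100 (10) | 0.99 | 0.40 | 0.42 | 0.01 |
| 105 (10) | 0.85 | 0.11 | 0.24 | 0.00 |
| 110 (10) | about 0.50 | 0.01 | 0.11 | 0.00 |
| 112.5 (10) | 0.40 | 0.00 | 0.09 | 0.00 |

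For a narrow distribution centred in the window (112.5, SD 6) the pooled corrected figure is about 0.06, close to the nominal 5%. Repeat runs differ by a few points. Taking the widest, the per-group ranges are about 6–74% corrected and 0–6% uncorrected.

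**Step 2. Rounding.** Recording FBS in whole units raises the rate because of ties. At 112.5 (SD 6) it goes from 6% to 56%, and at 110 (SD 10) from 48% to 87%. That increase comes from rounding, not from the entry window, so the table uses unrounded values.

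**Step 3. Baseline flagged, week 8 not flagged (test run by visit, corrected).** At n = 168 this happens in 0.71–0.94 of trials for a skewed or uniform baseline with change SD 5–10. It happens in 0.13–0.51 for a centred baseline or change SD 3. At n = 42 the range is 0.05–0.66.

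**Step 4. Do the listed transformations help?** Across the window the functions are close to straight lines. The ratio of their slopes at 100 and 125 is:

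- square root: 1.25^(1/2) = 1.12
- cube root: 1.25^(2/3) = 1.16
- log: 125/100 = 1.25
- reciprocal: 1.25² = 1.56

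Functions this nearly linear cannot undo a cut at both ends. In the pooled corrected test, raw and all four transformed versions fail together in 0.93–1.00 of trials when the parent mean is at or below 100. At mean 105 (SD 10) it is 0.61, against 0.85 for raw alone. At 110 (SD 10) it is 0.31, against 0.48. So the cure often fails but not always. The same near-linearity explains why the FBS p-value changes little between scales.

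**Step 5. Zeros.** The lowest DASS-21 subscale score is 2 × (7 × 0) = 0. log(0) and 1/0 are undefined; the square root and cube root of 0 are 0.

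**Step 6. HOMA-B, which affects the remedy.** The formula as printed is insulin × 360 / FBS − 63. With insulin 10 and FBS 110 (assumed), 10 × 360 / 110 − 63 = 32.7 − 63 = −30.3. A log cannot be taken of a negative value.

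**The case against.** The strongest reply is that the text is ambiguous rather than wrong. A variable could mean the outcome at both visits together, and naming a paired t-test and a repeated measures ANOVA already presupposes one scale. The word appropriate could be taken to exclude any function that is undefined for the data, which leaves square root and cube root for DASS-21. The statistical analyzer is blinded, which limits steering of the scale, though the coded groups A to D remain distinguishable. Nothing rules out back-transformation, and the FBS p-value hardly moves.

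Much of this stands, and it limits the point. It does not rescue the trigger itself, which the article states positively and which examines variables instead of residuals or differences. That is a rule badly fixed, not a detail left to a later document.

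A reader might infer several stronger things that the article does not support:

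- **That the entry window forces a transformation of baseline FBS.** Step 1 runs from near certainty to near zero, depending on the unknown distribution, on pooling and on the version of the test.
- **That no listed transformation can repair a flagged baseline.** In some simulated trials one does.
- **That the visits are certain to get opposite instructions.** The article does not say that the test is run by visit.
- **That PSQI scores would be lost.** The article does not state the PSQI minimum.
- **That a known number of women would be lost from DASS-21.** An assumed 10–30% with zero scores would give 168 × 0.10 = 17 to 168 × 0.30 = 50, but no such percentage appears in the article.
- **That the answer on synergy is at risk.** Dependence of interaction on scale is general, and none of the five questions under Study design is an interaction contrast.

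**Conclusion.** The point holds as a defect of the stated rule. The test looks at the wrong quantity, and for the primary outcome it can respond to eligibility instead of model failure. Under a pooled, Lilliefors-corrected test at n = 168 with unrounded values, that is likely (about 85–100%) if FBS values pile up near 100, about even at a parent mean of 110, and no more than nominal if values are centred and narrow. Tested per group it is about 6–74%, or 0–6% uncorrected. All of these rest on assumed FBS distributions.

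The consequence for the primary outcome is an unclear scale and possibly an effect in non-clinical units, not a materially different p-value. For DASS-21, choosing log or reciprocal would remove zero scorers from the intention-to-treat analysis, while square root or cube root would not. The wording should be changed before analysis, but the point does not threaten the primary test.

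**What to change.** Delete the Kolmogorov–Smirnov trigger and name one scale for each outcome, used at both visits:

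- FBS untransformed, with the effect in its clinical units.
- Strictly positive, skewed outcomes such as insulin, HOMA-IR and triglycerides on the log scale, reported as back-transformed ratios. Their skewness is a judgement; the article gives no data on it.
- DASS-21 and PSQI on their raw scores, with robust or bootstrap confidence intervals, so that no zero is lost.
- HOMA-B not logged unless the printed formula is first checked, since it can be negative.

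Use residual plots only as a check. The cost is a short change of wording, with no extra data or participants. The analyst gives up the freedom to choose a scale after seeing the data.

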### Objectives

Compare the mean serum lipid (triglycerides [TG], total cholesterol [TC], low-density lipoprotein cholesterol [LDL-C], high-density lipoprotein cholesterol [HDL-C]) and glucose indices (fasting blood sugar [FBS], fasting blood insulin [FBI], homeostasis model assessment - insulin resistance [HOMA-IR], homeostasis model assessment - beta cell function [HOMA-B]) between the four groups and within each group, before and after intervention.Compare the means of anthropometric indices (weight, waist circumference, body mass index [BMI]) and systolic and diastolic blood pressures between the four groups and within each group, before and after the intervention.Compare the mean scores of the Depression Anxiety Stress Scale (DASS-21) and Pittsburgh Sleep Quality Index (PSQI) between the four groups and within each group, before and after intervention.Determine the relationship between changes in mean level of serum vitamin D and each of the glucose indices, serum lipids, and the mean scores of the DASS-21 and PSQI between the four groups and within each group, during intervention.

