### Study outcomes

#### Primary outcomes

The primary outcome of this clinical trial is the difference in FBS in eight weeks between double placebo, vitamin D, omega-3, and double active groups from baseline to the post-intervention visit.

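### Within-arm before-after tests use a baseline FBS and vitamin D sample that also decided entry, so regression to the mean can make them significant with no treatment effect

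*Protocol article*

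**What the plan says.** **Tests.** The Objectives ask for comparisons "between the four groups and within each group, before and after intervention". All four objectives contain a within-group element, and the first three are before-after comparisons. The Statistical analysis section gives the test: "To compare the mean differences within each group, before and after intervention, the paired t-test will be used for continuous variables". The same section plans repeated-measures ANOVA, which "will be used to assess time effects and time-by-treatment (vitamin D and/or omega-3) interaction effects on all outcome variables between groups". Significance is set at p < 0.05. The section also says that all p values will be Bonferroni-corrected, in a sentence that refers to multiple endpoints and five pairwise comparisons. Nothing labels the within-arm tests as descriptive.

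**Entry and baseline.** Eligibility requires "FBS 100–125 mg/mL" and vitamin D below 32 ng/mL. Under Study participants, the women invited are "Women of reproductive age with prediabetes from Karaj health centers diagnosed with FBS test", so an earlier reading in the window comes first. Then: "At the beginning, 10 mL of blood will be taken from a peripheral vein after a 12-h overnight fast to assess plasma glucose levels", with vitamin D measured in the same draw. The next step is restricted by that result: "After three days, women who have been confirmed as having prediabetes (fasting glucose 100–125 mg/mL", together with the vitamin D limit. No other blood sample before treatment is described. The Abstract and the Assessments section mention only one sample at the start and one at the end.

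**Efficacy question.** The primary outcome is "the difference in FBS in eight weeks between double placebo, vitamin D, omega-3, and double active groups from baseline to the post-intervention visit". The five questions listed under Study design all compare one treatment with another or with placebo.

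**The concern.** A woman enters only if her measured FBS lies between 100 and 125. If most women in the source population have usual values below 100, those who qualify include a surplus whose reading was high by chance on the day. That same reading is then their before value. Eight weeks later the chance part is not repeated, so the arm mean falls whatever the women took. Vitamin D, selected to be low, would drift upward in the same way. HOMA-IR and HOMA-B are computed from FBS and inherit the shift: FBS multiplies in the first and stands in the denominator in the second.

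A paired t-test cannot separate this drift from an effect. The time term of the repeated-measures ANOVA cannot do so either.

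What is at stake is interpretation. A report could show a significant fall in an active arm and none on placebo, with no difference between the arms. Equally, it could show an apparent improvement on double placebo.

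**Working it through.** The protocol states no figure on this point, so there is none of its own to reproduce. The check is how often a paired t-test is significant in an arm with no effect.

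**Inputs from the protocol.** Entry window 100 to 125, applied to an earlier reading and again to the baseline sample; 38 women per arm (Sample size section); significance level 0.05, or 0.05/5 = 0.01 if the Bonferroni rule for five comparisons covers these tests.

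**Assumed inputs.** Population mean FBS, between-woman SD and within-woman SD. The protocol gives none of them, so a range is used.

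**Model.** Each reading is the woman's usual value plus independent error: screen S = T + e0, baseline B = T + e1, week 8 F = T + e2, with no treatment effect. Both S and B must lie in 100 to 125. The expected change is E(F − B) = −E(e1 | selected), which is negative when the population mean lies below the middle of the window.

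**One case by hand.** For mean 92, between-woman SD 8 and within-woman SD 5, simulation gives a mean change of −2.32 with SD 6.55.
- Standard error: 6.55/√38 = 1.063.
- Expected t: 2.32/1.063 = 2.18.
- Critical t on 37 degrees of freedom: 2.03 at 0.05.
- Chance of a significant fall: about Φ(2.18 − 2.03) = Φ(0.15) = 0.56. Simulation gives 0.57.

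**Simulated results, no effect, one arm of 38:**

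| Mean, between SD, within SD (assumed) | Mean change | Significant fall at 0.05 | at 0.01 |
|---|---|---|---|
| 92, 8, 6 | −3.26 | 71% | 46% |
| 92, 8, 5 | −2.32 | 57% | 32% |
| 95, 10, 5 | −1.47 | 26% | 10% |
| 98, 10, 4 | −0.79 | 14% | 4% |
| 105, 8, 5 | −0.79 | about 10% | about 3% |
| 112, 7, 5 | −0.06 | about 3% | below 1% |

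The nominal rate in that direction is 2.5% at 0.05 and 0.5% at 0.01. A wider grid (mean 90 to 95, between-woman SD 8 to 10, within-woman SD 3 to 7) gives 12% to 89% at 0.05. The earlier screen already softens the drift: for mean 90, SD 8 and within-woman SD 5, the change is −2.6 with it and −4.2 without.

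**The misleading pattern.** If p is the rate per arm, at least one of the three active arms shows a significant fall while placebo does not with probability (1 − p)[1 − (1 − p)³].
- p = 0.14: 0.86 × (1 − 0.636) = 0.31
- p = 0.26: 0.74 × (1 − 0.405) = 0.44
- p = 0.57: 0.43 × (1 − 0.080) = 0.40
- p = 0.71: 0.29 × (1 − 0.024) = 0.28

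**Between-arm check.** In the same no-effect simulations, a two-sample test of change between two arms rejects in about 5% of trials (4.5% to 6% over all scenarios run). The drift is the same in expectation in every randomised arm and cancels.

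**The case against.** The strongest reply is that the protocol does not use the paired tests to judge efficacy. The primary outcome and the five design questions are between arms, and the treatment question goes to the time-by-treatment term. A reader might infer that the paired tests are planned as tests of treatment effect, or that arms will be ranked by which reach significance. No sentence says so, and that reading should not be pressed. Nor is randomisation undermined, because the between-arm comparison keeps its error rate and the double-placebo arm is there to expose a non-specific fall.

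A reader might also infer that false falls are certain. They are not: the size rests on assumed inputs, the first four rows of the table place the population mean below the entry window, and a mean of 112 gives essentially no inflation.

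The Bonferroni sentence may cover the paired tests, since it speaks of all p values. That lowers the rates but leaves them well above 0.5% in the scenarios with means of 92 to 98.

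Finally, the selection argument does not extend to every outcome. Lipids, anthropometry, blood pressure, DASS-21 and PSQI were not used to select women on these two measurements.

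All of this limits the point. What remains is that within-arm change is a stated objective with a stated significance test, on a baseline that was itself the selection value. This is something that the protocol fixes, not a detail left to a later analysis plan.

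**Conclusion.** The point holds in limited form. For FBS, the HOMA indices and vitamin D, the planned paired t-tests and the repeated-measures time effect can be significant without any treatment effect, on double placebo as on active treatment. For FBS the false-fall rate in one arm is about 14% to 71% at 0.05 for assumed means of 92 to 98, about 10% at 105, and nominal at 112. These figures assume normal, independent errors, equal within-woman SD at each reading and 38 women per arm. The direction for vitamin D follows from its one-sided entry limit; its size was not calculated. The primary between-arm comparison and the sample size stand. The matter is worth correcting because it affects how results will be read, but it does not threaten the main analysis.

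**What to change.** In Objectives and Statistical analysis:
- Replace the tested within-group comparisons with descriptive reporting: mean change per arm with its 95% confidence interval and no p value. The section already promises 95% confidence intervals.
- Treat the repeated-measures ANOVA time effect in the same way.
- State that all efficacy conclusions, including those for secondary outcomes, rest only on the between-arm (time-by-treatment) contrasts.

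The cost is wording only, with no extra women, visits or loss of power for the between-arm comparisons. The downside is that the report will carry no within-arm p values, which some readers may expect.

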### Randomization method and intervention process

Eligible participants will be randomly divided into treatments with either double placebo, vitamin D alone, omega-3 alone, or double active (vitamin D and omega-3) groups according to the stratified block randomization. Block randomization is done in equal block sizes of four to ensure balance between groups. Stratified randomization will be used to control serum vitamin D level (vitamin D < 20 ng/mL, range = 20–32 ng/mL) [28] distribution. Any individual who is not involved in trial data collection and analysis carries out randomization. The intervention allocation will be blinded to the study investigators, participants, and the statistical analyzer.

Zahravi Pharmaceutical Company (Tabriz, Iran) produced vitamin D and omega-3 supplements and placebos. This was approved by the Food and Drug Administration. The appearance of the placebo capsule was indistinguishable in color, shape, size, packaging, smell, and taste from vitamin D and omega-3 capsules. The type of supplements in each group will be blinded as A, B, C, and D packages for investigators, participants, and the statistical analyzer.

Participants will receive supplements in four groups for eight weeks:
Vitamin D placebo every two weeks + 1000 mg omega-3 containing 360 mg eicosapentaenoic acid (EPA) and 240 mg docosahexaenoic acid (DHA) twice a day;50,000 IU vitamin D every two weeks + omega-3 placebo twice a day;50,000 IU vitamin D every two weeks + 1000 mg omega-3 twice a day;Vitamin D placebo every two weeks + omega-3 placebo twice a day.

At the beginning of the study, participants will receive the supplements. Previous studies have not reported any side effects from the supplements [22, 23]. Compliance of the participant to the intervention will be measured using capsule count and capsule log record. Their potential complications and consumption processes will be registered (number of consumed capsules and the returned packages). In addition, the consumption process will be checked once a week by telephone and any occurrence of adverse events will be recorded. Participants will be asked to keep their usual lifestyle including nutrition and physical activity level (Additional file 1).

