### Assessments and measurements

Participants will be visited at the Shahid Rastravesh Health Center three times, at baseline, after three days and after eight weeks. Participants will be interviewed regarding their sociodemographic background at baseline.

Then, at the beginning and eight weeks after the intervention, the following will be done:
Blood sample will be drawn after at least 12 h of fasting. All blood samples will be centrifuged at 3000 rpm for 10 min and serum will be separated into clean tube aliquots and stored at – 80 °C until analysis [12]. Collection of blood, specimen storage, and laboratory tests will be conducted at the Shahid Rastravesh Health Center laboratory in Karaj. To determine FBS, serum triglycerides, TC, and HDL-C concentrations, we will use an enzymatic kit (Pars Azmun, Tehran, Iran). LDL-C will be estimated based on the Friedewald equation [27]. Serum level of vitamin D and insulin will be quantified using a commercial enzyme-linked immunosorbent assay kit (Monobind, CA, USA).The HOMA-IR and HOMA-B will be determined according to suggested formulas [29].

$$ \mathrm{HOMA}-\mathrm{IR}=\left[\mathrm{FBI}\ \left(\upmu \mathrm{U}/\mathrm{mL}\right)\mathrm{x}\ \mathrm{FBS}\ \left(\mathrm{mg}/\mathrm{ml}\right)\right]/405 $$
$$ \mathrm{HOMA}-\mathrm{B}=\left[\mathrm{FBI}\ \left(\upmu \mathrm{U}/\mathrm{mL}\right)\ \mathrm{x}\ 360/\mathrm{FBS}\ \left(\mathrm{mg}/\mathrm{ml}\right)-63\right]\% $$

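### With two visits, the primary RM ANOVA is a change-score ANOVA without baseline FBS or the vitamin D stratum, so it gives up precision at no saving; Mauchly's test is wrongly named as a variance check

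*Protocol article*

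**What the plan says.** The protocol article defines the primary outcome, under Primary outcomes, as "the difference in FBS in eight weeks between double placebo, vitamin D, omega-3, and double active groups from baseline to the post-intervention visit". Assessments and measurements has blood drawn twice: "at the beginning and eight weeks after the intervention, the following will be done". The visit three days after baseline has no further blood draw, so each woman has two FBS values for analysis.

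Statistical analysis names one between-group model for every outcome. It is RM ANOVA with a Bonferroni adjustment for five comparisons, applied to time effects and to "time-by-treatment (vitamin D and/or omega-3) interaction effects on all outcome variables between groups". No covariate is named. Yet Randomization method and intervention process states: "Stratified randomization will be used to control serum vitamin D level", with strata below 20 and 20–32 ng/mL.

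On assumptions, Levene's test is assigned to the one-way ANOVA, which the section uses for baseline comparisons. For the repeated measures model it says that Mauchly's "test in RM ANOVA will be used to test homoscedasticity".

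**The concern.** A change score fixes the regression slope of week-8 FBS on baseline FBS at 1. The slope will be lower here. A single fasting glucose value varies within a woman, and participants are selected on that value: first by the health-centre test, then by the study's own sample, both within 100–125. When the true slope is below 1, subtracting the whole baseline value adds noise that ANCOVA would not.

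The stratum raises a similar question. The trial balances on vitamin D level, and the article's Discussion says that low levels go with higher fasting glucose. If the stratum predicts week-8 FBS, leaving it out of the model forgoes precision that the stratification made available.

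The Mauchly statement is a plain error about what the test does. It leaves the primary model without any named check of equal variances between groups.

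What is at stake is the precision of the primary comparison and a correct statement of the assumption checks. Validity is not at stake.

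**Working it through.** **The plan's own figure.** Sample size gives means and SDs of 86.8 ± 6.40 and 94.6 ± 10.30, 5% type I error and 80% power. S1² + S2² = 40.96 + 106.09 = 147.05, the difference is 7.8, and (1.96 + 0.8416)² = 7.849. So n = 7.849 × 147.05 / 60.84 = 18.97, that is 19, or 20 with the t distribution. The stated 20 reproduces. The root-mean-square SD is √(147.05/2) = 8.57. These are SDs of FBS levels. The 38 completers per group are taken as stated, and alpha for each comparison is 0.05/5 = 0.01.

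**The test is a change-score ANOVA.** Let d be a woman's change. With two visits and equal groups:
- interaction sum of squares = ½ Σ n(d̄_group − d̄)², on 3 df
- within-woman error sum of squares = ½ Σ(d − d̄_group)², on N − 4 df

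The halves cancel, so F equals the one-way ANOVA F on d. On simulated data (42 per group, two visits) both F values were 3.2372.

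**Precision, simplest case.** With the same SD s at both visits and baseline–week-8 correlation rho:
- variance of change = 2(1 − rho)s²
- ANCOVA variance = (1 − rho²)s²
- ratio = (1 + rho)/2, which is 0.65, 0.75 and 0.85 at rho 0.3, 0.5 and 0.7

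The ratio never exceeds 1. The document does not give rho, and this case ignores the restricted baseline range.

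**Precision with restricted baseline.** Assumptions, none of them in the document: between-woman SD 8–10, within-woman SD 4–6, and two qualifying FBS values in 100–125. Simulated slopes were 0.52–0.77. Four combinations gave the variances below. Power uses the noncentral t with 38 per group, two-sided alpha 0.01 and noncentrality = difference / √(2V/38).

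| Var(change) | Var(ANCOVA) | Ratio | Power for 4 units, change / ANCOVA | Power for 7.8 units, change / ANCOVA |
|---|---|---|---|---|
| 29.6 | 27.6 | 0.93 | 71% / 75% | 99.98% / 99.99% |
| 42.9 | 38.7 | 0.90 | 51% / 57% | 99.4% / 99.7% |
| 44.7 | 41.0 | 0.92 | 49% / 53% | 99.2% / 99.6% |
| 60.0 | 53.5 | 0.89 | 35% / 40% | 95.7% / 97.5% |

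Worked example, second row: √(2 × 42.9/38) = 1.503 and 4/1.503 = 2.66 for change; √(2 × 38.7/38) = 1.427 and 4/1.427 = 2.80 for ANCOVA.

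Letting the population mean also vary over 100–110 gives ratios of 0.87–0.93, a gain of 7–13%. In sample-size terms that is 38 × 0.07 = 2.7 to 38 × 0.13 = 4.9, or about 3 to 5 women per group.

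**Stratum.** This was a separate simulation with untruncated SD 8.57, a 4-unit effect, 38 per group and alpha 0.01. If the stratum shifts week-8 FBS by an assumed 0.5 SD, adding it to ANCOVA raises power from 28% to 31% (rho 0.3), 34% to 38% (rho 0.5) and 53% to 60% (rho 0.7). If it has no effect, power is unchanged (for example 39.0% v 39.1% at rho 0.5). Type I error was 0.5–1.3% for all three models over 3,000 runs per setting.

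**Mauchly's test.** With k visits there are p = k − 1 within-woman contrasts, and the test has p(p + 1)/2 − 1 df. For k = 2 this is 1 × 2/2 − 1 = 0. Sphericity holds trivially, so nothing is tested. For any k the test concerns the covariance structure across visits, not equality of variance between groups.

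**The case against.** The strongest defence is that nothing here threatens validity. Randomisation makes the change-score contrast unbiased, type I error stays near its nominal level, and the analysis matches an outcome defined as change. The first two points stand. The third does not count against ANCOVA: regressing change on group and baseline gives the same group coefficient as regressing the week-8 value on them, so the target of estimation is kept.

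Three stronger readings are tempting, and the document does not support them.

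- **The trial is underpowered for its planned difference.** A reader might put the planning SD of 8.57 at both visits, assume rho = 0.3, and find change-score power for 7.8 units of 76%. The article gives no rho, and that case ignores the eligibility range. In the range-restricted scenarios the change SD is 5.4–7.7, below the planning SD, and power for 7.8 is at least 95.7%.
- **Women without a week-8 value are excluded.** Classical RM ANOVA needs both values, and the article says "The effect of the intervention on all participants will be assessed based on intention-to-treat and per-protocol analyses". But it states neither exclusion nor imputation. A missing-data rule may sit in the full protocol or the SAP, which are not shown, and imputation before RM ANOVA would be compatible with the text.
- **Unequal variances distort the error rates of the contrasts.** The planning SDs of 6.40 and 10.30 do differ. They cover only two of the four arms, are SDs of levels rather than change, and come from another trial. Any figure for actual alpha would need invented SDs for the single-supplement arms.

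The benefit of the stratum is also conditional. It depends on the stratum predicting week-8 FBS once baseline FBS is in the model, which the article does not show.

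**Conclusion.** The point holds as a matter of precision plus one error of fact. The planned primary test is an unadjusted change-score ANOVA that leaves out baseline FBS and the randomisation stratum. It is unbiased but never more efficient than ANCOVA. The gain from adjusting for baseline is probably modest, about 7–13% of variance. For a 4-unit effect that is roughly 4 to 6 percentage points of power; for the planned 7.8 units it is at most 2. These sizes rest on the assumed between- and within-woman SDs, and the stratum's contribution on an assumed effect. That ANCOVA is at least as precise does not depend on those SDs, apart from the negligible cost of estimating one slope.

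The statement about Mauchly's test is wrong whatever the data show. The change is worth making because it costs nothing in the conduct of the trial, but the planned analysis is not invalid.

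**What to change.** In Statistical analysis, replace RM ANOVA as the between-group model for FBS and each other continuous outcome. Use ANCOVA of the week-8 value on the four treatment groups, with the baseline value of that outcome and the vitamin D stratum (below 20 v 20–32 ng/mL) as covariates. Take the five Bonferroni-adjusted comparisons from this model. Where an outcome is transformed, use the same transformation for its baseline covariate.

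Delete Mauchly's test. In its place, check residual variance between groups, for example with Levene's test on the ANCOVA residuals, and use robust standard errors if the variances differ.

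The cost is a change of wording. Baseline values and the stratum are already collected, and no visit, measurement or participant is added.
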